## Abstract

**Background:**

Clustering mental, physical and oral conditions reduce drastically the life expectancy. These conditions are precipitated and perpetuated by adverse social, economic, environmental, political and healthcare contextual factors, and sustained through bidirectional interactions forming potentially a ‘syndemic’. No previous study has investigated such potential syndemic. Thus, the present project aimed to (i) test for syndemic interactions between social adversity (socioeconomic adversity and traumatic events) and mental, physical and oral multimorbidity using the syndemic theoretical framework; and (ii) determine whether the syndemic relationships vary by age, sex and ethnicity.

**Methods:**

Data from three large-scale population-based databases: UK BioBank, US National Health and Nutrition Examination Survey (NHANES) and the Research with East London Adolescents Community Health Survey (RELACHS) will be analysed. Structural equation modelling (SEM) will be utilised to conceptualise syndemic factors and model complex relationships between directly observed and indirectly observed (latent) variables (syndemic constructs).

**Discussion:**

the syndemic conceptualisation provides a valuable framework to understand health and illness, and hence to better design and deliver effective and cost-effective preventative and curative integrated (syndemic) care to improve patient and population health. Such syndemic care aims to address the social determinants of health, whilst simultaneously managing all interlocked conditions.

## Introduction

The relationship between social adversity and mental, physical and oral multimorbidity is a topical yet under-researched area. A recent critical review proposed that such relationship is likely to form a syndemic (1). The review built its argument on the fact that mental disorders, physical multimorbidity and oral diseases share the same social determinants and have bidirectional relationships that are likely to have synergistic effects in terms premature mortality and excessive burden of morbidity (1–4).

Syndemics are defined as “the aggregation of two or more diseases or other health conditions in a population in which there is some level of deleterious biological or behaviour interface that exacerbates the negative health effects of any or all of the diseases involved” (5). Such adverse disease interactions can occur amongst all types of diseases infectious or non-communicable. They emerge in populations that experience social adversities such as poverty, stigmatisation, systemic discrimination and violence.

Though used interchangeably to describe the co-existence of multiple conditions in any given population, the syndemics concept goes beyond the concepts of comorbidity and multimorbidity. ‘Comorbidity’ describes the co-occurrence of additional conditions alongside a primary ‘index’ condition (6). ‘Multimorbidity’ refers to several conditions that co-exist in tandem but there is no single focus of attention on one condition over the others (7). However, ‘syndemics’ emphasise the adverse interaction between co-occurring diseases (bio-bio interaction) and underscore the role of precipitating and perpetuating adverse social, economic, environmental, political and healthcare contextual factors. These factors cluster with the myriad of diseases and shape their interaction (bio-social interaction) (8). Both types of interaction (bio-bio and bio-social) should exist to form a syndemic. The nature of these interactions should be “synergistic” rather than “additive”; meaning that the produced disease burdens are far more than the sum of disease burdens of each condition or factor alone. A few studies have operationalised the above syndemic concept correctly (8, 9).

Social adversity precipitates and exacerbates clusters of mental and physical diseases and conditions (**Figure 1**). For example, socioeconomic adversity (such as having low income, being unemployed or living in a deprived area) and traumatic events (such as adverse childhood experiences, being a victim of physically violent crime or sexual assault) are linked to compounded mental and physical conditions via systemic inflammation and behavioural pathways (10, 11). The situation can be further compounded by barriers to accessing healthcare (12). For instance, people with severe mental illness may experience under-recognition and under-treatment of physical conditions such as cardiovascular disease (12–14). In turn, these clustering mental and physical conditions reinforce each other through bidirectional interactions, that are also shaped by the social and contextual factors, leading to multiplicated mortality and morbidity burdens (8).

**Figure 1 f1:**
[figure not shown]
Theoretical framework to test for syndemic interactions between social adversity and mental, physical and oral multimorbidity.

Oral diseases could be a key element in the above social adversity, mental and physical syndemic. They share the same social determinants and have bidirectional interactions with mental and physical conditions, precipitating and perpetuating their personal, social and economic impacts (1, 15). For example, the higher rates of oral diseases and conditions, such as dental caries, periodontal disease and tooth loss, and the increased risk of the late detection of oral cancer in people with mental disorders compared to the general population are alarming (16–18). Poor oral health affects simple daily functions such as eating, smiling and socialising, and increases social stigma and limited employment opportunities experienced by people with mental disorders (19–21). Oral conditions were the 3^rd^ most common reason for preventable hospital admissions in people living with severe mental illness (22). Indeed, people with mental disorders considered improving their oral health as part of bouncing back to normality (23).

Singer et al. underscored the importance of conducting further studies to explore new syndemics (8). Zahid et al. called for future studies to explore further specific potential syndemics involving mental disorders (24). No previous study has investigated the potential syndemic relationship between social adversity and mental, physical and oral multimorbidity (1, 25). Thus, the primary aim of the present work is to test for syndemic interactions between social adversity (socioeconomic adversity and traumatic events) and mental, physical and oral multimorbidity using the theoretical framework depicted in **Figure 1**. The secondary aim is to determine whether the syndemic relationships vary by age, sex and ethnicity.

## Methods

To achieve the above aims, data from three large-scale population-based databases: UK BioBank, US National Health and Nutrition Examination Survey (NHANES) and the Research with East London Adolescents Community Health Survey (RELACHS) will be used. The following summarises research questions and data analysis plan for each dataset.

### UK BioBank research questions

UK BioBank database will be used to answer the following research questions:

Are there syndemic relationships between social adversity and mental, physical and oral multimorbidity impacting mortality burden and all-cause hospitalisation?Do these syndemic relationships vary by age, sex and ethnicity?

### UK BioBank methods

The present project’s methodology builds on published advances in testing the syndemic theory and personal communications with scholars working currently on testing the syndemic theory using UK BioBank data.

#### Design and study population

UK Biobank database comprises prospective biomedical data from 502,412 participants living across the UK and aged between 40 and 69 years at the time of recruitment (2006 to 2010). It benefits from data linkages to other health related records: primary care data, hospital admission data and cancer and death registries.

#### Syndemic outcomes

The syndemic outcomes are premature mortality and all-cause hospitalisation. Mortality data are obtained from the death register based on death certificates held within the NHS Digital (England and Wales) and the NHS Central Register (Scotland) between 01/01/2011 and 30/09/2021. All-cause hospitalisation data are obtained from the Hospital Episode Statistics data - Admitted Patient Care (England), Scottish Morbidity Records – General / Acute Inpatient and Day Case Admissions (Scotland), and Patient Episode Database (Wales) between 01/01/2011 and 28/02/2018.

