#### Covariates

Covariates are demographic variables: age, sex and ethnicity.

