#### Statistical analysis

Descriptive statistics will be used to summarise participants characteristics. For NHANES and RELACHS data, survey analysis procedures will be used to account for the sample weights, stratification and clustering of the complex sampling design to ensure representative estimates.

To answer the research questions on the presence of syndemic relationships, a structural equation modelling (SEM) technique will be utilised to conceptualise syndemic constructs and model complex relationships between directly observed and indirectly observed (latent) variables. The SEM technique has gained increasing popularity in syndemic research (30, 31). To use this technique, the following steps will be undertaken:

In step one, exploratory and confirmatory factor analyses will be used to identify the clustering nature and reduce the number of indicators (observed variables) under each theoretical construct. In step two, a SEM to predict premature mortality and all-cause hospitalisation, controlling for age, sex and ethnicity, will be run. Analysis will include identifying whether the indicators chosen to measure the latent constructs are acceptable. confirmatory factor analysis will be used to provide information on how indicator items measure underlying (latent) constructs. In step three of the analysis, SEM will be used to examine the direct and indirect relationships between the constructs. The goodness of fit (GoF) of the SEM model to the data will be assessed considering the indices of Comparative Fit Index (CFI) and Tucker-Lewis Index (TLI; where values >.90 indicate a good fit), root mean square error of approximation (RMSEA), and Standardised Root Mean Square Residual (SRMR; where value <.05 indicate a good fit). In step four, the synergistic (multiplicative) interactions between different latent constructs and measured variables will be tested using two-step estimation procedures (32).

To answer the question on whether syndemic relationships vary by age, sex and ethnicity, stratified analyses by age, sex and ethnicity will be performed.

Full Information Maximum Likelihood technique will be used as a pragmatic approach for data missing estimation for SEMs. This approach produces unbiased parameter estimates and standards errors (33). For UK BioBank and RELACHS datasets, stability of exposure data over time will be checked by calculating the intraclass correlation coefficients between baseline and follow up data.

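### UK BioBank all-cause hospitalisation rests on a Scottish source limited by name to general and acute care, the other nations' sources are not so limited, and nation is not in the model

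*Protocol article*

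**What the plan says.** The UK BioBank Syndemic outcomes section states: "The syndemic outcomes are premature mortality and all-cause hospitalisation". It then names one admission source for each nation:

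- England: "Hospital Episode Statistics data - Admitted Patient Care (England"
- Scotland: "Scottish Morbidity Records – General / Acute Inpatient and Day Case Admissions (Scotland"
- Wales: "Patient Episode Database (Wales) between 01/01/2011 and 28/02/2018"

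No second Scottish source is listed, and one date window serves all three. The Design and study population section gives "502,412 participants living across the UK" without a split by nation.

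The UK BioBank Covariates section reads: "Covariates are demographic variables: age, sex and ethnicity". Step two of the Statistical analysis section repeats this set ("controlling for age, sex and ethnicity, will be run"), and the planned stratified analyses use the same three variables. Nation appears in none of these places.

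**The concern.** An outcome described as all-cause should count the same kinds of admission wherever a participant lives. As named, the Scottish source covers general and acute care only, while the other two have no stated limit by type of care. If the names reflect the contents, the same admission history could be recorded as an event in one nation and as no event in another.

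This matters more here than for a generic outcome because mental multimorbidity is one of the constructs under test, and in UK BioBank it includes severe mental illness (F20-F29 and F31). Psychiatric admissions are the obvious candidates to fall outside a general and acute file. If they do, the missed events are related to an exposure of interest.

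Nothing in the plan would repair this. Full Information Maximum Likelihood deals with values known to be missing, whereas an admission outside the linked file is recorded as no admission. With no term for nation, even an average difference in capture between nations stays in the pooled model.

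**Working it through.** **What the text establishes.** Set side by side, the three source names differ in one respect: only Scotland's has a qualifier by type of care. The outcome label has none. The lists for covariates, model adjustment and stratification all omit nation.

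**What it does not establish.** The article does not say which admissions the Scottish file leaves out, whether the English and Welsh files include psychiatric care, or how many participants live in Scotland. It states no event rate or effect size for hospitalisation, so there is no figure to reproduce. The calculation below only shows scale, and every input is an assumption.

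**Inputs (all assumed)**

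- True risk of any admission: p1 = 0.60 with mental illness, p0 = 0.50 without. True risk ratio (RR) = 0.60/0.50 = 1.20; true odds ratio (OR) = (0.60/0.40)/(0.50/0.50) = 1.50.
- Scottish share of participants: s = 0.05 to 0.15.
- Share of hospitalised people with mental illness whose only admissions lie outside general and acute care: q = 0.02 to 0.20.
- Full capture in England and Wales, and in people without mental illness everywhere.

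**Formulas.** Observed pooled risk with mental illness = p1 × (1 − s × q). Within Scotland = p1 × (1 − q). Each is divided by p0 for the RR.

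| s | q | Pooled risk | Pooled RR | Pooled OR |
|---|---|---|---|---|
| 0.05 | 0.02 | 0.5994 | 1.199 | 1.496 |
| 0.05 | 0.20 | 0.5940 | 1.188 | 1.463 |
| 0.10 | 0.10 | 0.5940 | 1.188 | 1.463 |
| 0.15 | 0.02 | 0.5982 | 1.196 | 1.489 |
| 0.15 | 0.20 | 0.5820 | 1.164 | 1.392 |

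Within Scotland alone:

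| q | Risk | RR | OR |
|---|---|---|---|
| 0.02 | 0.588 | 1.176 | 1.427 |
| 0.10 | 0.540 | 1.080 | 1.174 |
| 0.20 | 0.480 | 0.960 | 0.923 |

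The pooled risk in people with mental illness is understated by s × q, that is by 0.05 × 0.02 = 0.1% up to 0.15 × 0.20 = 3%.

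**Interactions.** Take mental by physical multimorbidity on the ratio scale, with interaction = (p11 × p00)/(p10 × p01), where the first index is mental and the second physical.

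- If the same share q is missed in everyone with mental illness, p11 and p10 are both multiplied by (1 − s × q). The factor cancels and there is no bias.
- If people who also have physical multimorbidity are likelier to have at least one general or acute admission, fewer of them are missed and the ratio rises. With s = 0.10, q = 0.20 for mental illness alone and q = 0.02 for both, the interaction is multiplied by (1 − 0.002)/(1 − 0.020) = 0.998/0.980 = 1.018.

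The bias can therefore be nil or upward on this scale. On an odds scale the cancellation in the first case is not exact.

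**The case against.** The strongest reply is that the contents of the files are being inferred from their titles. That stands. A reader might infer that the plan excludes psychiatric admissions in Scotland and takes every admission in England. The documents say neither: the first is read from a title and the second from the absence of a qualifier. Both need to be verified.

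Second, the window is long: 01/01/2011 to 28/02/2018 is seven years and two months, in people aged 40 to 69 at recruitment. If the outcome is any admission, a person is missed only if they had no general or acute stay in all that time. The mental construct also covers mood disorder codes, not only psychotic illness. This argues for the lower end of q and for a small pooled effect. It has less force if admissions are counted, because each non-acute stay would then be lost.

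Third, several stronger readings are tempting but unsupported:

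- That interactions are biased downward. The working shows they may be unaffected or biased upward.
- That UK BioBank lacks a design correction the other datasets receive. The sentence "For NHANES and RELACHS data, survey analysis procedures will be used to account for the sample weights, stratification and clustering" concerns complex survey sampling. Nothing in the article describes UK BioBank as such a sample or mentions recruitment sites, so there is no basis for clustering standard errors by site.
- That nation confounds the adversity path through deprivation mix or coding practice. The article gives no figures on either.
- That the mental construct itself is under-recorded in Scotland. The source of its ICD-10 codes is not stated, and primary care linkage is also available.

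Finally, an extra sensitivity analysis could be left to a fuller plan. That is fair for the analysis alone, but this article itself names the sources and the covariates, and the mismatch lies there.

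**Conclusion.** The point holds as a limited one. The outcome label and the Scottish source name do not match, the restriction applies by name to one nation only, and nation is absent from adjustment and stratification. Capture of admissions may therefore differ by nation.

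A bias in the path from mental multimorbidity to hospitalisation follows only if psychiatric or other non-acute admissions lie outside the Scottish file and inside the others. In that case the bias is plausibly towards the null. On the assumed inputs the pooled effect is small (RR 1.20 to between 1.199 and 1.164), and it is concentrated in Scotland, where the RR would be 1.176 to 0.96. The direction for interactions, which are the plan's main interest, cannot be fixed from the documents. This is an inexpensive improvement to comparability and does not threaten the study's conclusions as a whole.

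**What to change.** 1. In the UK BioBank Syndemic outcomes section, state how psychiatric and other non-acute admissions are handled in each national source.
2. Add nation to the UK BioBank covariates and to the adjustment set in step two. This absorbs an average difference in capture between nations. It cannot recover missed admissions or remove a difference by mental illness within Scotland, so it is not sufficient alone.
3. Then do one of the following: restrict the outcome to the same admission types in all three nations; add the matching Scottish records if they are linked; or pre-state a repeat of the hospitalisation model without Scottish participants.

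The cost is a clarifying sentence, one covariate and, under the last option, one more model run on a somewhat smaller sample. At the assumed Scottish share of 5-15%, that run would keep about 502,412 × 0.95 = 477,291 to 502,412 × 0.85 = 427,050 participants. Harmonising to the narrower admission types has its own cost: the outcome would no longer be all-cause and should be relabelled.

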#### Syndemic constructs

Syndemic constructs include social adversity (socioeconomic adversity and traumatic events) and mental, physical and oral multimorbidity.

Socioeconomic adversity will be measured by socioeconomic position (SEP) indicators at individual, household and neighbourhood (area) levels: education, employment, income and deprivation. Education is measured at an individual level and will be categorised into high (college/vocational training or above) and low (A levels, AS levels, or equivalent; O levels, GCSEs, or equivalent; CSEs or equivalent; NVQ, HND, HNC, or equivalent; other professional qualifications; and “none of the above”). Employment status is measured at an individual level and will be grouped into: employed (including those in paid employment or self-employed, or doing unpaid or voluntary work) and unemployed (including being retired, full or part time students, unemployed, looking after home and/or family, or unable to work because of sickness or disability). Income is measured by the annual total household income before taxes are deducted. It will be categorised into 0 (>£100,000), 1 (£52,000-£100,000), 3 (£31,000-£51,999), 4 (£18,000-£30,999), and 5 (<£18,000). Area deprivation is measured by Townsend deprivation index quintiles. The two quintiles with the highest area deprivation scores will be scored 1 (indicating high levels of area deprivation), and the rest of quintiles will be scored 0 (indicating low levels of area deprivation).

Traumatic events will include felt hated by family member as a child, did not feel loved as a child, physically abused by family as a child, sexually molested as a child, no one to take to doctor when needed as a child, victim of physically violent crime, victim of sexual assault, witnessed sudden violent death, belittlement by partner or ex-partner as an adult, physical violence by partner or ex-partner as an adult, sexual interference by partner or ex-partner without consent as an adult, and been involved in combat or exposed to war-zone.

Mental multimorbidity will include mood disorders and severe mental illness (ICD-10 codes: F20-F29; F31; F33-34).

Physical multimorbidity will be measured using Ronaldson et al. approach that comprises a total of 36 long term physical health conditions (**Supplementary Table 1**) (22).

Oral multimorbidity will include the presence of moderated to severe periodontal disease, toothache and use of denture. Self-reported painful gums and loose teeth will be used as surrogates for moderate to severe periodontal disease. In cases of multiple responses, the most severe indicator will be used as the primary surrogate for periodontal disease. Participants who did not report the above oral health indicators will be considered periodontally healthy.

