#### Syndemic constructs

Syndemic constructs include social adversity (socioeconomic adversity) and mental, physical and oral multimorbidity. No data is available in NHANES on traumatic events.

Socioeconomic adversity will be measured by SEP indicators at individual and household levels: education, employment, occupation, income and health insurance. Education is measured at an individual level and will be categorised into high (college or above) and low (high school diploma or below). Employment status is measured at an individual level and will be grouped into: employed (working at a job or business or with a job or business but not at work) and unemployed (looking for work or not working at a job or business). Occupation is measured using socioeconomic index, which is based on the employees’ earnings, education level and prestige. It will be categorised based on the median into upper and lower level and unemployment. The lower level will include retirees and students. Income is measured by family income ratio to the federal poverty line (<100%, 100%-199%, 200%-399%, >400%). Health insurance will be categorised into private health insurance (including any private health insurance, Medi-Gap or single-service plan), public health insurance only (including Medicare, Medicaid, State Children’s Healthcare Plan, military healthcare, Indian Health Service, State Sponsored Health Plan or other government programme) and no health insurance. No data is available in NHANES on area deprivation.

Mental multimorbidity will include depression (“moderately-severe” or “severe” depressive symptoms versus “moderate”, “mild” or “no” depressive symptoms; as measured by the PHQ-9) and severe mental illness (as measured by medicines prescribed in the past month for severe mental illness).

Physical multimorbidity will be measured using Ronaldson et al. approach (**Supplementary Table 1**) (28). However, not all the 36 long term physical health conditions are reported in NHANES (such as bronchiectasis, psoriasis and polycystic ovarian syndrome). Only those that are available in NHANES will be used to indicate the physical multimorbidity construct.

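### The UK BioBank employment indicator scores retired, student, homemaking and sick or disabled participants as unemployed, so the adversity construct partly reflects age and existing illness

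*Protocol article*

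**What the plan says.** **Concept.** The Introduction of the protocol article gives unemployment, next to low income and a deprived neighbourhood, as its example of socioeconomic adversity. It does not name retirement, study or incapacity.

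**UK BioBank methods, Syndemic constructs.** Employment is dichotomised. One side is "employed (including those in paid employment or self-employed, or doing unpaid or voluntary work"; the other is "unemployed (including being retired, full or part time students, unemployed, looking after home and/or family, or unable to work because of sickness or disability". The cohort was "aged between 40 and 69 years at the time of recruitment (2006 to 2010"). Physical and mental illness are separate constructs in the same section.

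**NHANES methods, Syndemic constructs.** Employment and occupation are both indicators. On employment the adverse side is "unemployed (looking for work or not working at a job or business"). Occupation has an upper level, a lower level and unemployment, and "The lower level will include retirees and students".

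**Statistical analysis.** Factor analyses reduce and check the indicators, the outcome model controls for age, sex and ethnicity, analyses are also stratified by these three, and step four tests multiplicative interactions between latent constructs.

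**Two other UK BioBank codings.** After code 0 for the top band, income continues "1 (£52,000-£100,000), 3 (£31,000-£51,999), 4 (£18,000-£30,999), and 5 (<£18,000"). Education is "high (college/vocational training or above") against a low group that contains "NVQ, HND, HNC, or equivalent; other professional qualifications".

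**The concern.** The primary aim is to test whether social adversity interacts with mental, physical and oral multimorbidity, and the Introduction requires both bio-bio and bio-social interaction before a syndemic is claimed. That distinction needs an adversity measure that does not already contain the diseases. A person too ill to work is counted once through the multimorbidity constructs and again as socially adverse. A comfortably pensioned retiree is also scored adverse, while an unpaid volunteer is not.

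Deaths and admissions are counted from January 2011, after recruitment ended in 2010. People already too sick to work at recruitment could therefore produce a path from adversity to mortality or admission without any social mechanism, and a bio-bio effect could be reported as bio-social.

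**Working it through.** The plan states no figure on this point, so there is none to reproduce. The check has four parts.

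**1. What the coding puts into the interaction.** Let U, R, H and S be mutually exclusive 0/1 markers for unemployed, retired or student, looking after home, and sick or disabled. The planned indicator is E = U + R + H + S. If the employment item enters the adversity score with weight w, the product of that score with multimorbidity M contains w·S·M, which is illness times illness, and w·R·M, which for retirees brings in age. The weight w is unknown. It is zero only if the item is dropped.

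**2. Composition of the flagged group (assumed shares).** Assumptions: retired 10 to 40%, unemployed 2 to 5%, sick or disabled 2 to 5%, student or home 3%. Each share is the group divided by the total flagged. Selected rows:

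| Retired | Unemployed | Sick | Flagged | Retired, of flagged | Unemployed, of flagged | Sick, of flagged |
|---|---|---|---|---|---|---|
| 10% | 5% | 5% | 23% | 10/23 = 43% | 22% | 22% |
| 10% | 2% | 5% | 20% | 50% | 10% | 25% |
| 10% | 5% | 2% | 20% | 50% | 25% | 10% |
| 20% | 5% | 5% | 33% | 61% | 15% | 15% |
| 40% | 2% | 2% | 47% | 40/47 = 85% | 4% | 4% |

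Over the whole grid, 17 to 53% of participants are flagged. Of those flagged, 4 to 25% are truly unemployed and 4 to 25% are sick or disabled.

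**3. Does age adjustment repair it? (simulation, assumed inputs)** 500,000 people, age uniform from 40 to 70. Retirement depends on age only, unemployment on a latent adversity independent of age, and incapacity on an illness score that rises with age. The resulting shares are 26.8% retired, 3.3% unemployed and 2.2% sick.

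| Correlation of the indicator with | Age | Illness | True adversity |
|---|---|---|---|
| Flag as planned | 0.63 | 0.20 | 0.06 |
| Flag after linear age adjustment | – | 0.06 | 0.08 |
| Unemployed only, retired and sick set aside | 0.00 | 0.01 | 0.20 |

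Age adjustment removes most of the correlation with illness. What remains (0.06) is close to the correlation with the adversity that the item is meant to measure (0.08).

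**4. The other codings.**
- NHANES: a retiree is not working at a job, so falls on the adverse side of employment, but is placed in the lower occupational level, apart from unemployment. An unemployed person is adverse on both indicators. The two items therefore share variance by construction and disagree about retirees.
- Income: codes 0, 1, 3, 4, 5 have steps 1, 2, 1, 1. With equal bands, the correlation with 0 to 4 is 13.0/√(17.2 × 10) = 0.991. Two other assumed distributions give 0.986 and 0.989. The effect is nil if income is treated as ordinal.
- Education: vocational training is high, while NVQ, HND, HNC and professional qualifications are low. Vocational qualifications thus fall on both sides of the split.

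**The case against.** The strongest reply is that the plan has safeguards. Factor analysis may discard a weak employment item, and an item that correlates 0.06 with true adversity would be a candidate. Age is controlled, and analyses are stratified by age. This stands in part: nobody has estimated the item's loading, and the simulation shows that age adjustment does real work. But factor analysis selects on shared variance. Retirement and incapacity plausibly lower household income as well, so the item could equally be kept. Neither age control nor age strata remove sickness from the indicator.

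A second reply is that exclusion from work through illness is itself adversity. The Introduction describes bidirectional links and mentions restricted employment opportunities for people with mental disorders. This stands. It is why counting only job-seekers as adverse cannot be presented as the one correct coding, and why a sensitivity analysis is needed.

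A reader might also infer more than the documents support:
- That the flagged group is mostly retirees. There are no counts, and within the assumed range the share falls to 43%.
- That the income and education codings add to the age and illness problem. They are separate slips and do not cause it.
- That the coding has been shown to create a false interaction. It has been shown only that it could contribute one. The simulation did not test an interaction.

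For NHANES, the employment item does not name retirees. Their place there is inferred from their not working at a job.

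**Conclusion.** The point holds for the employment coding. It follows from the definitions: an indicator meant to measure unemployment also takes in retirement and incapacity, and incapacity overlaps with the constructs with which adversity is to be interacted. Age control reduces the age part and leaves an illness part, so an interaction of adversity with multimorbidity could not be read cleanly as bio-social.

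The size of the bias cannot be determined from the documents. The composition figures rest on assumed shares. The correlations rest on a simulation in which adversity is independent of age and illness, so they are illustrations. The NHANES overlap is real but secondary. The income numbering has almost no numerical effect (correlation about 0.99), and the education split is an ambiguity of unmeasured effect.

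**What to change.** - **UK BioBank employment.** Keep separate categories: employed; unemployed; retired or student; looking after home; unable to work through sickness or disability. Do not score retirees and students as adverse, and state how those looking after home are scored. Leave sickness or disability out of the adversity indicator in the primary model, and state whether these participants then take a non-adverse or a missing value on this item. They remain in the model through education, income and area deprivation. Report a sensitivity analysis that puts sickness or disability back in.
- **NHANES.** Use one combined employment and occupation indicator, so that unemployment counts once and retirees are neither unemployed nor lower level.
- **Minor corrections.** Number the income bands 0 to 4. Place vocational, NVQ, HND, HNC and professional qualifications so that the high and low definitions agree.

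The cost is recoding of variables already held and one extra analysis. The adverse employment group becomes smaller, the primary construct loses illness-related exclusion from work, and people who retired early through ill health would be scored non-adverse. The sensitivity analysis covers incapacity but not those early retirees, so this limitation should be stated.
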